## Abstract

**Background:**

There is limited evidence to assess if interventions implemented during pregnancy proactively mitigate parental vaccine hesitancy and promote timely vaccination among children after birth. This study protocol describes the evaluation of an ADaptivE PrenaTal (ADEPT) intervention to increase childhood vaccinations that is implemented with first-time pregnant individuals (PIs).

**Methods:**

Within the framework of a type 1 effectiveness-implementation hybrid study design, a cluster-randomized trial (CRT) will determine the effectiveness of ADEPT at increasing childhood vaccinations, and a nested explanatory mixed methods (NMM) study will assess changes in parental vaccine hesitancy. Study practices will be randomized to deliver ADEPT in addition to standard of care or standard of care alone. Providers at intervention sites will participate in a 4-part training program on childhood vaccines and effective communication. During a routine prenatal visit, providers will discuss vaccines recommended for the PI during pregnancy and for the child after birth, following which PIs will be screened for vaccination intention. Vaccine-hesitant PIs will be offered adaptive components of the intervention, which include an educational website and phone call with a vaccine navigator to discuss concerns. They will also be offered enrollment into the NMM study, where their vaccination intention will be assessed post-intervention. After PIs give birth, their child’s vaccination outcomes at 2 months will be extracted from the state immunization registry. The primary study outcome is the difference in timely childhood vaccination at 2 months between the intervention and control arms. The secondary outcome is reduction in vaccine hesitancy assessed among PIs in the NMM study as the pre-post intervention change in vaccination intention.

**Discussion:**

The study findings are expected to contribute evidence on the effectiveness of prenatal interventions to proactively mitigate parental vaccine hesitancy and promote timely vaccinations after the child’s birth.

**Trial registration:**

The study protocol is registered in ClinicalTrials.gov (NCT05795855).

## Background

Among children born in the United States (US) from 2020–2022, an estimated 30% were not up-to-date with recommended vaccines by 24 months of age [1]. Prior publications have documented varied patterns of adherence to the recommended vaccination schedule in the US, including delayed and selective vaccination, and refusal of all vaccines [2–4]. Delayed vaccinations increase the period that children remain at risk for preventable infections such as measles and polio, and efficacy of vaccine protection is reduced when all recommended vaccine doses are not received [2]. Findings from a 2022–23 survey by the American Academy of Pediatrics suggest an increase in requests to deviate from the recommended vaccine schedule, with a majority (>90%) of surveyed pediatricians reporting such requests from at least one family in their practice in the 12 months preceding the survey [5].

Parents express a variety of reasons for delayed or refused vaccinations among children, including concerns about vaccine safety, complacency toward vaccine-preventable diseases, and concerns about the number of vaccines a child gets in a single visit [6, 7]. Concerns about the number of vaccines in particular have been compounded by the introduction of novel vaccines and therapeutics in the US childhood vaccination schedule, including the mRNA-based COVID-19 vaccine annually starting at 6 months of age, and a monoclonal antibody injection for infants <8 months old to protect against Respiratory Syncytial Virus (RSV). In a Pew Research survey, half of parents of children aged 0–4 years were somewhat concerned about the necessity of all recommended vaccines [8]. Since recommended vaccines protect children from serious, and sometimes deadly, infections, responding to parental concerns is critical for supporting timely vaccinations and reducing preventable childhood morbidity and mortality.

Pregnancy is an under-utilized time for parental vaccine education. In a 2022 survey focused on pregnant individuals in prenatal practices associated with one academic medical center in North Carolina, we found only 67% with an intention to accept all vaccines (not inclusive of the COVID-19 vaccine) for their child after birth, and only 35% with an intention to accept COVID-19 vaccines for their child, when eligible [9]. Existing interventions aimed at reducing parental vaccine concerns focus on the pediatric primary care setting, in the period after the child is born [10–12]. Since vaccines are routinely recommended during the prenatal setting for the pregnant individual, there is an opportunity to expand vaccine conversations during pregnancy to address childhood vaccinations [13–15]. Routine prenatal care includes multiple interactions with the healthcare system that present opportunities for timely intervention on childhood vaccination. However, there are no guidelines in the current standard of care for the inclusion of childhood vaccine conversations during pregnancy [14–16]. In addition, prenatal care providers are rarely prioritized for formal education about childhood vaccines [17]. In a survey conducted in April 2022, prenatal providers identified time constraints during appointments and training gaps on childhood vaccines as top barriers to implementation of a childhood vaccination intervention [18]. Evidence on the effectiveness of prenatal interventions that incorporate provider training and account for constraints on provider time is needed to transform clinical practice guidelines for inclusion of childhood vaccine conversations.

This protocol describes plans to implement and evaluate an ADaptivE PrenaTal (ADEPT) intervention to increase childhood vaccinations. ADEPT is a multi-component adaptive intervention designed to support first-time pregnant individuals (PIs) in their decisions around vaccinations in pregnancy and for the child after birth. This protocol describes key features of the ADEPT intervention and plans for its evaluation in a type 1 effectiveness-implementation hybrid study.

## Methods

The evaluation of the ADEPT intervention is described in accordance with the SPIRIT schedule of enrollment, interventions, and assessments (**Fig 1** and **S1 File**) [19]. Prospective recruitment of study practices started on April 27, 2024, and is expected to be completed by January 31, 2025.

**Fig 1 pone.0313742.g001:**
[figure not shown]
SPIRIT schedule of enrollment, interventions, assessments for the ADEPT study. Activities related to practices, providers, and pregnant individuals.

### Description of the intervention

The ADEPT intervention components are described in accordance with the template for intervention description and replication (TiDieR) checklist (**S2 File**) [20]. The core and adaptive components of ADEPT are shown in **Fig 2**. The core component of ADEPT is a prenatal provider recommendation in favor of maternal and childhood vaccinations. Adaptive components include a multimedia educational website and phone consultations with a vaccine navigator. These components are described below.

**Fig 2 pone.0313742.g002:**
[figure not shown]
ADEPT core and adaptive components.

#### Core component

The core component of ADEPT is a vaccine recommendation by prenatal providers to first-time PIs at the end of the second trimester (26–32 weeks), encouraging vaccinations during pregnancy and for their child after birth. Prior to intervention implementation, providers at intervention sites will complete four training sessions on the following topics: overview of the routine vaccination program in the US (including COVID-19 vaccine and RSV immunization recommendations), vaccine clinical trials and safety, and strategies for effective communication (2 sessions). During active implementation, prenatal providers will make recommendations encouraging timely maternal and childhood vaccinations.

#### Adaptive components

The ADEPT intervention consists of two adaptive components: a multimedia vaccine education website and phone consultations with a vaccine navigator. The assignment of the adaptive component is determined based on a screening questionnaire that will assess vaccination intention, that is administered after the core component is delivered to the PI. PIs who have a positive vaccination intention will not receive any adaptive intervention components. PIs who are in favor of vaccinations but exhibit some degree of hesitancy (e.g., plan to delay some vaccines) will be offered access to the multimedia vaccine education website. PIs with negative intention to vaccinate or those unsure of their decision will be offered access to the multimedia vaccine education website, as well as a phone consultation with a vaccine navigator.

Multimedia vaccine education website: An educational website was co-developed with parents. The website includes the following sections: About Us, About Vaccines, Vaccine Preventable Diseases, About the Schedule, Vaccination Schedule, Vaccines During Pregnancy, Visit Detail, What Doctors Say, Research with Confidence, Vaccines by Numbers, and More Resources. The ‘More Resources’ tab includes links to other credible websites such as cdc.gov and the American Academy of Pediatrics’ Healthy Children webpage for those interested in learning more. PIs without sufficient access to the internet or an internet-enabled device, may request access to a handout with the website content. Such individuals will also be reassigned automatically to receive a phone consultation with a vaccine navigator.Vaccine Navigator: The navigators are members of the study team and will connect with eligible PIs via phone. The vaccine navigators will participate in the provider trainings described with the core component of the intervention. The purpose of the navigator is to respond to questions or concerns not addressed by the website or during provider recommendation.

### Study design overview

ADEPT will be evaluated using a type 1 effectiveness-implementation hybrid study design that includes a cluster randomized trial to assess effectiveness outcomes and a nested mixed method study to assess changes in parental vaccine hesitancy following exposure to the intervention [21]. The methods below are described in accordance with the Consort 2010 statement: extension to cluster randomized trials (**S3 File**) [22].

### Evaluation objectives

The primary objective of the evaluation is to determine the effectiveness of ADEPT at increasing timely childhood vaccinations compared to standard of care.

#### Cluster-Randomized Trial (CRT)

We will cluster-randomize 14 study practices in a 1:1 ratio to the intervention or control arm utilizing a covariate constrained randomization approach [23]. Practices in the intervention arm will implement the standard of care plus ADEPT whereas practices in the control arm will continue to implement the standard of care (no ADEPT, **Fig 3**). After the PIs in the intervention and control arms give birth, we will assess timeliness of the 2-month vaccines for the child using data from the state immunization registry. The primary study outcome will be the difference between the intervention and control arms in the timeliness of childhood vaccinations recommended for children at 2 months (see **Outcomes**).

**Fig 3 pone.0313742.g003:**
[figure not shown]
Practice and participant flow between the cluster randomized trial and nested mixed methods study.

#### Nested Mixed Methods (NMM)

The NMM study will follow an explanatory sequential design and include those PIs who are eligible to receive the adaptive intervention component(s) and who consent to research activities to provide feedback on the intervention. The quantitative component of the NMM study will consist of survey questionnaires, and the qualitative component will consist of in-depth interviews. The qualitative portion will occur after the quantitative data collection to help explain or elaborate on the quantitative findings. Specifically, the qualitative data will explore reasons for observed intervention effects and identify factors that can explain significant or non-significant findings. Using joint displays and narrative summaries, we will integrate qualitative and quantitative outcomes to explain any observed intervention effect [24].

### Study setting

The study will be conducted in prenatal practices affiliated with health departments and a large academic medical center located in North Carolina. Practices may include diverse prenatal providers including obstetricians, family medicine practitioners, midwives, nurse practitioners, and physician assistants. The expected annual birth cohort is approximately 5,800 babies at the academic medical center, irrespective of first-time parent status.

### Participants and eligibility criteria

The prenatal practices will be those based in North Carolina and who provide routine prenatal care to PIs. Childhood vaccination discussions with PIs should not be part of practice standard of care for eligibility.

Prenatal providers will include those working in intervention practices. There are no exclusions by provider type or training.

PIs will be first-time pregnant individuals who receive routine prenatal care in study practices. PIs who are at a high risk of preterm delivery will be excluded to ensure there is adequate time to deliver the adaptive intervention components. High risk pregnancy will include multiple pregnancy, known fetal congenital malformations or genetic abnormalities, or documented as at-risk by the prenatal provider. Due to the timing of the ADEPT core component, PIs will be in their late second trimester during intervention exposure. For the NMM, vaccine hesitant PIs who are at least 18 years of age, provide informed consent for enrolment in NMM, and plan to stay in the study area for at least 3 months after delivery, will be eligible.

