#### CRT

Representatives from each practice will complete a survey to provide data on the practice-level covariates necessary for constrained randomization and to assess readiness for implementation of ADEPT. At the time of outcome assessment, study practices will utilize medical records to generate a list of first-time PIs who were in their second and third trimester during the study period. The linkage of these data to the state immunization registry will be used to determine vaccination outcomes for children post-delivery. Identifiable data will be managed by an honest broker who will communicate with the state immunization registry for receiving vaccination data. De-identified datasets will be shared with the study team by the honest broker for calculation of vaccination outcomes.

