### Statistical considerations

#### Sample sizes

*Provider trainings*. Only individuals from the intervention practices will be offered access to the trainings. All providers, staff and trainees at these practices will be eligible to participate in the training.

*CRT*. We anticipate the proportion of children who receive delayed or no vaccination at 2 months of age at baseline to be 20% [6]. We estimate that the intervention will reduce this proportion to 10%. We used a sample size formula for a two-sided Z-test comparing two proportions that accounts for the CRT design and incorporates a small-sample bias correction suitable for CRTs with fewer than 30–40 clusters in total (see equation (3) of Thomson et al, and more details in **S5 File**) [27]. With a sample size of 7 practices in each arm (14 total) and with at least 55 PIs/practice (770 total) the study would be powered at 90% to detect a difference in the proportion of 10% between arms at a two-sided alpha level of 5%, assuming that the coefficient of variation of cluster (i.e., practice-level) proportions with the primary outcome is 0.15 [27]. The target sample size is further inflated by 10% (total: 850) to accommodate a small reduction in power anticipated due to variable enrollment by practice and a small proportion of children with missing effectiveness outcomes due to out-of-state movement [28, 29]. In reality, the sample size for each practice will depend on practice size and eligibility of the PI population seen during the study period. Given that the primary outcome will be measured via data linkage of practice-level data to the state immunization registry using an honest broker, we will request an extract of data for all eligible PIs who are seen at the practice during the study period with the goal that the majority of enrolled practices would be expected to meet this target. Sensitivity analyses show that 80% power would be achieved if the proportion of children who delayed or refused vaccination at 2 months of age is 30% (rather than 20%) with a slightly smaller CV of 0.125 or even if the coefficient of variation is as large as 0.2 (**S5 File**).

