### Study strengths and limitations

There may be lower rates of vaccine-hesitant PI enrollment in the NMM study because of the reliance of self-selection. We plan to employ diverse recruitment methods (including patient portal messages, flyers, etc.) to help mitigate this risk. If lower enrollment is identified during tracking, higher usage of purposive recruitment methods may be used. In the unlikely event that reasonable balance in study practice characteristics is not achieved using the constrained randomization technique, the team will explore other statistical approaches to minimize confounding effects like adjusting for imbalanced covariates in statistical models. Despite exclusions of high-risk PIs, there is always the possibility of early delivery for participants (before 36 weeks) or patient drop-off, which leaves less time for implementation of the adaptive intervention components. However, clinician experts will evaluate the inclusion/exclusion criteria, and the research team will tailor analysis if such concerns arise. Lastly, due to the varying size of the practices, there may be variable recruitment rates and numbers. However, there is no reason to expect differential dropout rates between study arms. These potential problems are also accounted for in our sample size estimates by incorporating a 10% inflation rate.

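### The provider-documented at-risk exclusion is undated and discretionary, and nothing keeps labels or events after exposure from changing the primary cohort

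*Protocol article*

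**What the plan says.** All references are to the protocol article.

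- **Participants and eligibility criteria.** PIs at high risk of preterm delivery are excluded so that the adaptive components can be delivered in time. The definition reads: "High risk pregnancy will include multiple pregnancy, known fetal congenital malformations or genetic abnormalities, or documented as at-risk by the prenatal provider". The first two criteria are objective. The third is whatever the provider has documented, with no date and no list of conditions.
- **Core component.** The practice's own trained providers give the vaccine recommendation at 26-32 weeks. Providers in intervention practices therefore know the arm.
- **Recruitment, PIs.** A waiver of consent is sought for the trial outcomes, so no consent date fixes who is in the cohort.
- **Data collection, CRT.** "At the time of outcome assessment, study practices will utilize medical records to generate a list of first-time PIs" in their second and third trimester during the study period. The high-risk exclusion is not mentioned here.
- **Sample sizes, CRT.** The registry extract is to cover every eligible PI seen in the study period.
- **Data analysis, CRT.** The primary analysis uses children of all enrolled PIs, expressly including those in the intervention arm who screened as hesitant. The GEE model contains arm, strata and practice-level covariates, and individual-level adjustment is said to be impossible.
- **Study strengths and limitations.** Early delivery before 36 weeks is acknowledged as something that may happen to participants, and then: "clinician experts will evaluate the inclusion/exclusion criteria, and the research team will tailor analysis if such concerns arise".

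**The concern.** In a cluster trial where practices know their arm and the individuals are listed after randomisation, the comparison is protected only if the same people would be listed whichever arm the practice was in. An exclusion that depends on a provider's judgement, has no cut-off date and serves a purpose that exists in one arm only does not give that protection. The open wording on adapting the analysis adds a second route by which events after exposure could change who is counted.

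At stake is the primary comparison. If PIs were removed differently by arm and those removed differed in vaccination timeliness, the estimate would shift. The planned model could not correct this, because it adjusts only for practice-level characteristics. The article's statement that differential dropout is not expected concerns loss of participants, not who is counted as eligible.

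**Working it through.** **1. The plan's own figure.** Inputs from Sample sizes, CRT: 20% delayed or no vaccination against 10%, m = 55 PIs per practice, coefficient of variation 0.15, two-sided alpha 5%, power 90%. The equation cited in the article is not shown, so a standard cluster formula with one added cluster per arm as the small-sample correction is assumed:

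c = 1 + (1.960 + 1.282)² × [0.20×0.80/55 + 0.10×0.90/55 + 0.15²×(0.20² + 0.10²)] / 0.10²

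= 1 + 10.507 × (0.002909 + 0.001636 + 0.001125) / 0.01 = 6.96, that is 7 practices per arm.

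Power with 7 per arm is 90.2%. Inflation: 770 × 1.10 = 847, stated as 850. The design figures reproduce, and this point does not affect them.

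**2. When the exclusion is applied.** Set side by side, the eligibility section gives the criterion without a date. The data-collection section gives the time of listing without the criterion. The sample-size section says eligible and the analysis section says enrolled, but no dated entry point common to both arms is described. The timing of the exclusion is therefore not fixed. Applying it at list-building is one possible reading, and the text neither states nor excludes it.

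**3. Possible size (assumed rates).** The article gives no rate of at-risk labelling. Suppose there is no true effect, with non-timely proportion p = 0.20 in both arms. An extra share x of the intervention arm is removed, and those removed have non-timely risk q. Then

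spurious benefit = p − (p − xq)/(1 − x) = x(q − p)/(1 − x).

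| x | q = 20% | q = 30% | q = 40% | q = 50% |
|---|---|---|---|---|
| 2% | 0 | 0.2 | 0.4 | 0.6 |
| 5% | 0 | 0.5 | 1.1 | 1.6 |
| 10% | 0 | 1.1 | 2.2 | 3.3 |

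(percentage points in favour of ADEPT)

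Extreme case, q = 100% at x = 5%: 0.05 × 0.80/0.95 = 4.2 points. With 385 PIs per arm this means removing about 19 of the 77 non-timely PIs in the intervention arm, and no timely ones.

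**4. Effect on the test.** With the variance from step 1, evaluated at 20% and at 20% minus the bias, and 6 effective practices per arm, the two-sided type I error by normal approximation rises from 5% to about 5.9% at a bias of 1 point, 8.9% at 2 points and 14% at 3 points.

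**5. Removal that is equal in both arms.** If it is also unrelated to outcome, it costs only power: 87.9% at 50 PIs per practice, 85.0% at 45 and 81.4% at 40.

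**The case against.** A reader might infer that the plan applies the exclusion when the list is drawn, so that a PI counselled at 28 weeks and labelled at 33 weeks drops out of the primary cohort. The document does not say so. The data-collection section omits the exclusion, and the link rests on the word eligible in the sample-size section. The stated purpose of the exclusion looks forward, which fits a judgement made before the adaptive components. Early deliverers are still called participants, and adapting the analysis need not mean removing anyone. Hesitant PIs in the intervention arm are expressly kept in. Two of the three criteria are objective. Nothing shows that providers know what the label does to trial membership, or that they label differently by arm. An article may also leave the exact record query to the full protocol.

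Most of this stands, and it limits the point to what the rules allow. It does not remove it. A forward-looking purpose is not a cut-off date, and keeping PIs who screened as hesitant does not protect against a later at-risk label. The eligibility rule and the way the cohort is assembled are stated in the article itself, so this is not merely omitted detail.

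**Conclusion.** The point holds as a weakness in how the primary cohort is fixed. One eligibility criterion is discretionary and undated, its rationale operates in one arm only, the list is built by the practices at outcome assessment, and the handling of early delivery is left open. Together these permit exclusion after exposure, which the planned model cannot repair.

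It does not follow that such exclusion is planned or that bias will occur. Bias requires labelling that differs by arm and is related to vaccination timeliness, and the document gives no evidence of either. Direction and size cannot be derived from it. Under the assumed rates above, the spurious benefit is about 0.2-3.3 points against a design effect of 10 points, and zero if those removed resemble the cohort. The 4.2-point figure is a one-arm extreme in which every removed PI is non-timely, and it should not be read as an expected value. The change is worth making because it is cheap and closes the gap.

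**What to change.** - **Participants and eligibility criteria, and Data collection (CRT):** define trial eligibility identically in both arms from information recorded on or before a fixed gestational reference point, for example the start of the 26-32-week window or the index visit in that window. If the index visit is chosen, define it the same way for control practices. Use one common record query in all practices and ignore at-risk labels entered later.
- **Study strengths and limitations:** state that PIs who later become high-risk or deliver early stay in the primary analysis, and that any adapted analysis is a sensitivity analysis only.
- **Reporting:** give the number excluded by arm and by reason.
- **Optional:** let the honest broker, who already handles the identifiable data, apply the exclusions.

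The cost is some rewording and one record query. Some PIs who deliver early and miss the adaptive components will remain in the analysis, which slightly dilutes the estimated effect.
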